#### Intervention

Care partner participants randomized to the intervention group will receive the D-CHAT and usual care delivered through the patient’s care team. Aftercare partners complete the D-CHAT, and their responses will be given to the unit coordinator to review and make suggested referrals to specified clinicians. These clinicians then use the responses to develop and complete information and skill preparation with the care partners. For example, the D-CHAT could reveal that a care partner does not have the necessary diabetes knowledge or skill set to help give her husband living with Alzheimer disease and diabetes his insulin injections. Information gleaned from the D-CHAT would trigger a diabetes care and education specialist to address the care partners’ caregiving needs.

#### Usual Care Control

The comparison condition will be the usual care that hospitalized people living with dementia and their care partners receive as part of the large academic health care system. No standardized clinical decision-support tool that facilitates the identification and preparation of care partners is currently used for routine hospital-based dementia care. These care partner participants will complete the same measures as participants in the intervention condition on the same timeline using identical assessment procedures.

#### Measures

Participants will be assessed on the measures listed in Table 2. Participants will be compensated US $25 after each time point is completed. Baseline measures will be collected in person at the hospital, and follow-up assessments will be administered via phone by a study team member. The primary clinical outcome we will measure is a change in care partner preparedness. The Preparedness for Caregiving Scale [30] is a self-rated measure that consists of 8 items that ask care partners how well prepared they believe they are for multiple domains of caregiving. Preparedness is defined as perceived readiness for multiple domains of the caregiving role, such as providing physical care, providing emotional support, setting up in-home support services, and dealing with the stress of caregiving. Responses are rated on a 5-point scale, with scores ranging from 0 (not at all prepared) to 4 (very well prepared). The scale is scored by calculating the mean of all items answered with a score range of 0 to 4. The higher the score, the more prepared the care partner feels for caregiving. The items have an internal consistency rating of 0.88 to 0.93. We will also collect secondary outcome measures, including satisfaction of care, caregiving burden, and depression, using standardized measures.

#### Sample Size Justification

An estimated sample size of 128 will be recruited for the main trial based on the 95% CI width around the effect of the D-CHAT on care partner preparedness as measured by the Preparedness for Caregiving Scale [31]. Since this is a novel tool that will be adapted as part of phase 1, the variability of the response is unknown, and therefore justification is based on general terms of SD. With 64 subjects in both groups, the 95% CI width of the estimated effect will be 0.35 × SD. We expect to see a medium effect size (Cohen *d*=0.5). With this 95% CI width and expected effect size, we will have a sufficiently narrow CI of the true effect size to apply toward the planning of the future efficacy trial. If there was a ≈12% loss to follow-up such that 56 in each group have follow-up data, the 95% CI width would only increase to 0.375 × SD.

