#### Data Analysis

Analyses will be conducted using SAS (SAS Institute Inc) [32]. We will screen univariate distributions for normality and influential outliers and confirm that the randomization process balanced demographic characteristics between groups. We will also document the number of participants who are lost in each group, the reasons for the loss, and unintended crossovers. This information will influence the design of a future trial, including the frequency and mode of communication with clinicians and participants. The effect of the D-CHAT on care partner preparedness will be estimated as the difference in mean change from baseline to study completion between groups. The 95% CI will be calculated using a *t* distribution. Cohen *d* effect size will be calculated as the effect of the D-CHAT divided by the pooled standard deviation. This will give us a sense of the magnitude of the effect in terms of SDs. If normality assumptions in the raw data are not met and a simple transformation of the data (logarithmic or square root) does not sufficiently normalize the distribution, then we will use a nonparametric equivalent methodology [33]. If greater than 10% of the participants are noncompliant with their group assignment, then a per-protocol sensitivity analysis will be conducted to assess how influential the noncompliance was on the results of the study. Noncompliance is based on whether the group assignment was followed.

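### The 95% CI widths given to justify N = 128 are half-widths; the interval from 64 per arm is 0.70 SD wide, not 0.35 SD

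*Protocol article*

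**What the plan says.** The Protocol article, under Sample Size Justification, chooses the sample size for precision rather than power: "An estimated sample size of 128 will be recruited for the main trial based on the 95% CI width around the effect of the D-CHAT". Because "the variability of the response is unknown, and therefore justification is based on general terms of SD", everything is expressed in SD units. Two figures follow. The first is "With 64 subjects in both groups, the 95% CI width of the estimated effect will be 0.35 × SD". The second covers a loss scenario: "If there was a ≈12% loss to follow-up such that 56 in each group have follow-up data", then "the 95% CI width would only increase to 0.375 × SD". From the first figure and an expected Cohen d of 0.5, the section concludes that "we will have a sufficiently narrow CI of the true effect size" for use in planning the later efficacy trial.

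The Data Analysis section fixes what the interval is for. The effect is "estimated as the difference in mean change from baseline to study completion between groups", its 95% interval comes from a t distribution, and d is that effect divided by the pooled SD.

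**The concern.** The width of a confidence interval is the distance from its lower to its upper limit. For two groups of 64, an interval only 0.35 SD wide is implausibly tight, because the standard error alone is about 0.18 SD. The stated numbers look like the distance from the estimate to one limit.

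This matters because interval width is the stated basis for N = 128, and estimating the effect size is a declared aim of the pilot. Someone planning the efficacy trial from this text would credit the pilot with twice the precision it will have.

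**Working it through.** **Inputs**, all from the Protocol article:
- 64 per group, or 56 per group in the loss scenario (8/64 = 12.5%); expected d = 0.5 (Sample Size Justification).
- Two-group difference in mean change, with a 95% interval from the t distribution (Data Analysis).
- SD set to 1, since the section works in SD units. A common SD in the two groups is assumed.

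**Formulas**
- Half-width = t(0.975, 2n − 2) × SD × √(2/n)
- Full width = 2 × half-width

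**Reproducing the stated figures**

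| n per group | √(2/n) | t | Half-width | Full width | Stated width |
|---|---|---|---|---|---|
| 64 | 0.1768 | 1.979 (126 df) | 0.3498 SD | 0.6997 SD | 0.35 SD |
| 56 | 0.1890 | 1.982 (110 df) | 0.3745 SD | 0.7490 SD | 0.375 SD |

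Both stated figures match the half-width to rounding.

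**Other readings tried at n = 64**
- Normal quantile in place of t: half-width 0.346, full width 0.693.
- Two-sided 90% interval: full width 0.586.
- Interval for one group's mean: full width 0.500.
- Noncentral-t interval for d = 0.5: 0.147 to 0.851, width 0.704.
- One-sample interval on all 128 participants: full width 0.350. This matches, but it is not a between-group comparison.
- SD taken as the raw-score SD, with a smaller SD of change. A full width of 0.35 needs the SD of change to be half the raw SD. From √(2(1 − ρ)) = 0.5, this gives ρ = 0.875 as the pre-post correlation. The article states no such assumption and says the variability is unknown.

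No two-group interval in units of the SD of change has a full width of 0.35.

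**Expected interval at d = 0.5**
- As the text reads: 0.5 ± 0.175 = 0.325 to 0.675.
- 64 per group: 0.5 ± 0.350 = 0.15 to 0.85.
- 56 per group: 0.5 ± 0.375 = about 0.13 to 0.87 (noncentral t: 0.123 to 0.875).

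**What a full width of 0.35 SD would take**
- Normal approximation: n = 2 × (2 × 1.96/0.35)² ≈ 251 per group.
- With t: 253 per group, 506 in total. 253/64 ≈ 4 times the plan.

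**Consequence for planning.** As an illustration, I assume a two-sided 5% test with 80% power; the article does not give these values. Then n per arm ≈ 2 × (1.960 + 0.842)²/d² = 15.70/d².
- Limits implied by the text: 15.70/0.675² ≈ 35 to 15.70/0.325² ≈ 149 per arm.
- Limits the design delivers: 15.70/0.85² ≈ 22 to 15.70/0.15² ≈ 698 per arm.

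**The case against.** The strongest reply is that the calculation was right and only the word is wrong. Both figures match the t-based half-width to rounding, which suggests that ±0.35 SD was the precision actually worked out, and some authors use width loosely for half-width. On that reading N = 128 follows from the intended precision and nothing in the design changes. The section also sets no numerical target, so no threshold is missed. At d = 0.5 the interval excludes zero under either reading, and a pilot may reasonably accept 0.15 to 0.85.

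Much of this stands. N = 128 is not shown to be inadequate, and the 253 per group only measures the gap; it is not a size the trial should aim for. The 12% loss is a what-if scenario, not a planned rate. Whether 0.15 to 0.85 is narrow enough is a matter of judgement.

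The reply does not rescue the text. Nothing in the article tells the reader that width means half-width, and the plain reading is wrong by a factor of two in both places. If the adequacy claim was judged against ±0.35 SD, the article should say so; if it was judged against a total width of 0.35 SD, it has no support.

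**Conclusion.** The concern holds. The stated 95% CI widths of 0.35 and 0.375 SD are half-widths. The full widths are 0.70 SD with 64 per group and 0.75 SD with 56 per group, twice what is written. At d = 0.5 the limits run from a negligible effect to a large one.

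This rests on the article's own two-group t interval, equal groups, a common SD, and SD meaning the SD of change. It would fail only under a one-sample interval, which is not the planned comparison, or under an unstated pre-post correlation of about 0.87. The error lies in the stated precision and in the adequacy argument built on it. It does not show that the sample size or the planned analysis is invalid.

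**What to change.** Keep N = 128 and correct the Sample Size Justification along these lines:

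> With 64 per group, the half-width (margin of error) of the 95% CI is 0.35 × SD, a full width of 0.70 × SD. With 56 per group, the half-width is 0.375 × SD, a full width of 0.75 × SD. If the observed d is 0.5, the 95% CI would be about 0.15 to 0.85 with 64 per group and about 0.13 to 0.87 with 56 per group.

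State that SD means the SD of the change score. Then either explain why an interval of that size is enough to plan the efficacy trial, or delete the adequacy claim.

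The cost is wording only: no added participants and no change to the analysis. The price is a less favourable precision statement.

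### The stated 95% CI widths of 0.35 and 0.375 SD are half-widths, so the interval is twice as wide as written and does not support the claim that it is narrow enough to plan the efficacy trial

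*Protocol article*

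**What the plan says.** The Sample Size Justification of the Protocol article chooses the number of participants for precision, not power: "An estimated sample size of 128 will be recruited for the main trial based on the 95% CI width". It then gives the precision: "With 64 subjects in both groups, the 95% CI width of the estimated effect will be 0.35 × SD". Because the variability of the response is not known, "justification is based on general terms of SD". The expected effect is a Cohen d of 0.5, and from these two figures the section concludes that "we will have a sufficiently narrow CI of the true effect size to apply toward the planning of the future efficacy trial". It also allows for dropout of about 12%, leaving 56 per group, and says that in that case "the 95% CI width would only increase to 0.375 × SD".

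The Data Analysis section estimates the effect as the between-group difference in mean change from baseline, with a t-based 95% CI. It adds that the Cohen "effect size will be calculated as the effect of the D-CHAT divided by the pooled standard deviation".

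**The concern.** The sample size has one justification: the width of an interval, judged narrow enough for a stated use. If the number labelled as the width is only half of it, that judgement was made on an interval that looks twice as precise as the one the trial will deliver.

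The difference matters for the stated use. The required sample size varies with the inverse square of the effect size, so the lower limit of d dominates any planning range. A reader who takes 0.35 as the full width sees an interval of 0.325 to 0.675 around d = 0.5, which is a workable basis for planning. The interval that 64 per group can give starts near 0.15, and its limits span everything from a very small trial to a large one.

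**Working it through.** **Inputs from the protocol.** Sample Size Justification: 64 per group, or 56 after loss (1 − 56/64 = 12.5%); stated widths 0.35 SD and 0.375 SD; expected d = 0.5. Data Analysis: difference in mean change, 95% CI from the t distribution.

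**Inputs assumed.** Two-sided 5% and 80% power for the efficacy trial, with 90% as a sensitivity check. The protocol states none of these.

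**Step 1: reproduce the stated figures.** In units of the SD of the analysed variable, the half-width of a two-sample 95% CI is t(0.975, 2n − 2) × √(2/n).

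- n = 64: 1.979 × 0.1768 = 0.350
- n = 56: 1.982 × 0.1890 = 0.375

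Both figures match the protocol as half-widths. The full widths are 2 × 0.350 = 0.70 SD and 2 × 0.3745 = 0.75 SD. A full width of 0.35 SD would need about 2 × (1.96/0.175)² ≈ 251 per group, roughly four times the planned number.

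**Step 2: the interval at the expected effect.**

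- 64 per group: 0.5 ± 0.35 = 0.15 to 0.85. A noncentral-t interval for d gives 0.147 to 0.851.
- 56 per group: 0.5 ± 0.375 = 0.125 to 0.875.
- 0.35 read literally as the full width: 0.5 ± 0.175 = 0.325 to 0.675.

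**Step 3: what each interval implies for the efficacy trial.** Number per arm for a two-sample t-test at two-sided 5%, rounded up:

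| Interval for d | 80% power, lower limit | 80% power, upper limit | Ratio |
|---|---|---|---|
| 0.15 to 0.85 (64 per group) | 699 | 23 | about 30 |
| 0.125 to 0.875 (56 per group) | 1006 | 22 | about 46 |
| 0.325 to 0.675 (literal reading) | 150 | 36 | about 4 |

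At d = 0.5 itself the number is 64 per arm. At 90% power the first row becomes 935 and 31, and the second 1346 and 29.

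**Step 4: does the choice of SD rescue the claim?** Step 1 is in SDs of the change score. If the expected 0.5 were meant in SDs of the raw score, and the variances were equal at both times with correlation r (not in the protocol), the half-width would be 0.35 × √(2(1 − r)) raw-score SDs:

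- r = 0.3: 0.41, wider than 0.35
- r = 0.7: 0.27, so d runs from 0.23 to 0.77, or about 301 to 28 per arm in a raw-score comparison at 80% power
- r = 0.8: 0.22, so d runs from 0.28 to 0.72, or about 204 to 32 per arm

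Even at the higher correlations the range is 6- to 11-fold, still wider than under the literal reading.

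**The case against.** The protocol sets no threshold for a narrow enough interval, and comparing sample sizes at the two CI limits is a severe test because they scale with 1/d². The power and significance level used here are also assumed. All of that is true. But the protocol makes a positive claim of adequacy and supports it with a number whose label is wrong by a factor of two. The contrast between a 4-fold and a 30-fold range does not depend on a fine choice of threshold or power.

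Two stronger readings are tempting, and the documents do not support them.

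- **A reader might infer that the efficacy trial will be sized on the pilot point estimate.** The text says that the CI will be applied toward planning. The Data Analysis section gives d only the role of conveying magnitude, and it says that losses and crossovers will also inform the next design. Sizing on the point estimate is a risk, not a stated plan.
- **A reader might infer that d rests on an undefined SD, so that a systematic sizing error is built in.** The effect is a difference in mean change, so the pooled SD is naturally that of change, and on that reading 0.35 SD is consistent with the analysis. An error would arise only if a later planner put that d into a raw-score calculation, which the protocol does not propose. Naming the SD is also detail commonly left to the analysis plan, which is not shown. Moving to the baseline SD would detach d from the precision statement.

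It also stands that nothing in the conduct of this trial or in its primary estimate is affected.

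**Conclusion.** The point holds for the precision statement and for the conclusion drawn from it. The values 0.35 and 0.375 are correct as margins of error and wrong as widths; this follows from the protocol's own group sizes and CI method and needs no outside assumption. With d = 0.5 as the protocol expects, the interval is about 0.15 to 0.85, or 0.125 to 0.875 after the allowed loss. The translation into about 699 to 23 per arm (about 1006 to 22 after loss) rests on the assumed 80% power and two-sided 5%; at 90% power the range is of the same order. Such an interval does little to narrow the size of the next trial, so the claim of sufficient narrowness is not supported.

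This does not show that 128 is the wrong size for a pilot. Which SD standardises d is a minor clarification.

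**What to change.** In the Sample Size Justification:

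1. Restate the two figures as half-widths (margins of error) of 0.35 and 0.375 SD of the change score, and print the intervals they imply at d = 0.5: about 0.15 to 0.85 with 64 per group and 0.125 to 0.875 with 56.
2. Replace the sentence on sufficient narrowness with wording such as: *The efficacy trial will be powered on an important difference on the Preparedness for Caregiving Scale, stated in advance. The pilot will supply the SD of change, the correlation between baseline and follow-up scores, retention and adherence. The pilot effect and its CI will be used only to check that this difference is plausible.*

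As a small clarification in Data Analysis, say that the pooled SD is that of the change score. No move to the baseline SD is needed.

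The cost is wording and two descriptive statistics, the SD of change and the correlation. Both come from the two preparedness assessments already scheduled in Table 2, which also collects attrition and adherence. Sample size, conduct and data collection stay as they are. The downside is a more modest claim for the pilot and a less favourable precision figure in print.

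### The effect is estimated as an unadjusted change-score difference that in effect uses completers only; loss tied to baseline or outcome that also differs between arms would bias it, and a baseline model would reduce that risk

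*Protocol article*

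**What the plan says.** Protocol article, Sample Size Justification: "An estimated sample size of 128 will be recruited for the main trial". The precision statement is "With 64 subjects in both groups, the 95% CI width of the estimated effect will be 0.35 × SD". For a loss of about 12% it continues: "56 in each group have follow-up data, the 95% CI width would only increase", to 0.375 × SD. The resulting effect size is meant for planning the efficacy trial.

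Protocol article, Data Analysis: the effect is the "difference in mean change from baseline to study completion between groups". The interval is t-based ("The 95% CI will be calculated using a" t distribution), and no covariate is named. The same section commits to documenting how many are lost in each group and why, and states the use: "This information will influence the design of a future trial, including the frequency and mode of communication with clinicians and participants". It names one sensitivity analysis, a per-protocol analysis if more than 10% do not comply with their assignment. It names none for loss.

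Table 2 collects preparedness at both time points and lists attrition as a feasibility measure. Follow-up is a phone assessment within 72 hours of discharge.

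**The concern.** A participant without the follow-up call has no change score. The stated estimator therefore sets aside that person's baseline preparedness, which was measured before randomization. This is harmless when loss is unrelated to preparedness, or when it works the same way in both arms. It is not harmless when those reached differ from those lost in ways that differ by arm.

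That possibility deserves a check. The Introduction says that inadequately prepared care partners are at high risk of burden, stress and depression, so being reachable soon after discharge could depend on preparedness. Only the D-CHAT arm receives the extra referrals and skill preparation, so retention could differ. Neither is evidence that it will happen.

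At stake is the effect size, one of the main products of the pilot and an input to the size of the next trial.

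**Working it through.** **1. The plan's own figures.** The half-width of a 95% CI for a difference in two means is t(0.975, 2n−2) × SD × √(2/n).

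- n = 64 per group: 1.979 × 0.1768 = 0.350 SD.
- n = 56 per group: 1.982 × 0.1890 = 0.375 SD. Loss is 8/64 = 12.5%.

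Both stated figures reproduce, as half-widths. The second needs 56 completers per group, so the planned precision is that of completers. The acknowledged cost of loss is 0.375 − 0.350 = 0.025 SD.

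**2. When a completer difference is biased.** Let p be the share lost in an arm, and δ the completers' mean change minus the mean change of those lost, in SD. Then bias = p_I δ_I − p_C δ_C (I = D-CHAT, C = usual care). The δ values and any unequal split are assumptions; the documents give none.

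| Loss, one arm / other arm | δ, same order | Bias (SD) |
|---|---|---|
| 12.5% / 12.5% | 0.5 / 0.5 | 0 |
| 18.75% / 6.25% | 0 / 0 | 0 (half-width 0.3755) |
| 12.5% / 12.5% | 0.5 / 0 | 0.125 × 0.5 = 0.0625 |
| 18.75% / 6.25% | 0.5 / 0.5 | (0.1875 − 0.0625) × 0.5 = 0.0625 |

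Bias needs both parts: loss related to outcome, and a difference between arms in rate or mechanism.

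**3. Loss related to baseline preparedness.** Take SD 1 at both time points and correlation ρ. Expected change falls by (1 − ρ) for each SD of higher baseline, because of regression to the mean. Let D be the completers' mean baseline minus that of those lost. Completers in an arm then sit p × D above all those randomized to it, and

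bias = (1 − ρ) × (p_C D_C − p_I D_I).

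Assume 5% lost under D-CHAT, 20% under usual care (12.5% overall), and the same D in both arms. The bracket is 0.15 × D.

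- D = 0.9: 0.15 × 0.9 = 0.135; at ρ = 0.7, bias = 0.3 × 0.135 = 0.04 SD.
- D = 1.33: 0.15 × 1.33 = 0.20; at ρ = 0.3, bias = 0.7 × 0.20 = 0.14 SD.
- Milder selection, D = 0.5: 0.15 × 0.5 = 0.075; bias 0.02 SD (ρ = 0.7) to 0.05 SD (ρ = 0.3).

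The SD of change is √(2(1 − ρ)), which is 0.775 at ρ = 0.7 and 1.183 at ρ = 0.3. In SDs of change, the 0.04 to 0.14 range is therefore about 0.05 to 0.12. The direction here is upward: those lost under usual care have low baselines and would have gained most. With the heavier loss under D-CHAT, the sign reverses.

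**4. The same data with baseline modelled.** If loss depends only on baseline and arm, a model that estimates the baseline slope removes this bias. Simulation under the step 3 assumptions gives a bias near zero. The standard error relative to a change score is about √((1 + ρ)/2): 0.81 at ρ = 0.3 and 0.92 at ρ = 0.7. Allowing for unequal loss, the simulated gain is about 6% to 19%.

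**5. What a shift means for the next trial.** At 80% power and two-sided 5%, n per arm ≈ 2 × (1.96 + 0.842)² / d² = 15.7/d². For d = 0.5 this is 63. If a bias of 0.0625 made d read 0.5625, it would be 50.

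**The case against.** The best case for the plan has five parts.

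- **Missing-data policy belongs in the SAP or full protocol, which are not shown.** This stands for an imputation policy or a delta-adjusted analysis. It does not cover the estimator, which the article itself fixes as an unadjusted change-score difference.
- **The sizing sentence does not say that a wider interval is the only consequence of loss.** Correct. A reader might infer that from the word only, but it describes the size of the increase to 0.375 SD. The sentence is a sound statement about precision.
- **Loss is checked.** In part. A reader might infer that nothing is done, but numbers and reasons are recorded by group, so unequal loss would be visible. What is not stated is any use of that record to examine the effect estimate. Likewise, exclusion of those lost is inferred from the estimator and the 56 per group; the article does not state it.
- **Change scores subtract the baseline, so low baseline preparedness cannot bias them.** This fails unless ρ = 1. Change itself depends on baseline through regression to the mean, as step 3 shows.
- **The magnitudes are assumed, and only about 8 losses per arm are expected.** This stands. With 5% versus 20% lost and those lost doing 1 SD worse in change in both arms, a reader might infer a bias of 0.05 × 1 − 0.20 × 1 = −0.15 SD, or 30% of d = 0.5. The documents support neither the split nor the 1 SD. Nor do they support the view that outcome-related loss alone, or unequal loss alone, must bias the result.

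**Conclusion.** The point holds as a weakness in the chosen estimator; the article's precision arithmetic is not in error. A completer change-score difference is exposed to bias when loss is related to baseline or outcome and also differs between arms. Under strong assumed selection on baseline, with 5% versus 20% lost and ρ of 0.3 to 0.7, that bias is about 0.04 to 0.14 SD. It is 0.02 to 0.05 SD under milder selection, and zero if loss is random or acts alike in both arms. The upper values exceed the 0.025 SD widening that the article allows for, but stay well inside the 0.375 SD half-width. This does not invalidate the pilot. It is worth changing because a better estimator uses data already planned and is also more precise.

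**What to change.** In Data Analysis, make the main estimate a longitudinal model of baseline and follow-up preparedness with a common baseline mean across arms, including all randomized participants, or the equivalent baseline-adjusted analysis. Keep the completer change-score difference with its t-based interval as a secondary result. Report baseline preparedness of those lost, by arm, beside the numbers and reasons already planned. In Sample Size Justification, add that the 56-per-group figure addresses precision only.

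The cost is a little more analysis work and a few sentences; no new data, visits or participants are needed. The model still assumes that loss is explained by baseline and arm, and this should be stated. A delta-adjusted sensitivity analysis would probe that assumption but is optional in a pilot of this size.
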